#### *Local laboratory values*

Boxplots of local laboratory values by treatment will be generated for baseline values and for values measured during the course of the study. Each boxplot will show the 1st quartile, the median, and the 3rd quartile. Outliers, or values outside the boxplot, will also be plotted. If appropriate, horizontal lines representing boundaries for abnormal values will be plotted.

### 9.5.4 Immunogenicity analysis

The statistical analysis for immunogenicity will employ the intent-to-treat principle, i.e., all data from enrolled participants will be used according to the initial randomization assignment regardless of how many injections they received. The only exception will be to exclude data from HIV-infected participants at or post infection. Thus, for HIV-infected participants, only immunogenicity data from samples known to be drawn prior to HIV infection will be included in the analysis.

If assay data are qualitative (i.e., positive or negative) then analyses will be performed by tabulating the frequency of positive response for each assay by vaccine regimen at each time point that an assessment is performed. Binomial response rates will be presented with their corresponding exact 95% confidence interval estimates. For Parts A and B, crude rates for each vaccine group will be calculated. The combined placebo groups of Part B (N=18) will be used to estimate the false positive rate. Although, because of the lack of precision in this estimate, net response rates will not be calculated for the vaccine groups.

To compare the response rates of any two vaccine arms, a significant difference will be declared if the 2-sided 95% confidence interval for the difference in response rates between 2 groups excludes 0. In addition to reporting the point prevalence response rates, cumulative and cumulative repeat (over time/visit) probabilities of cellular immune responses will be estimated with corresponding confidence intervals using maximum likelihood based methods [102]. Missing responses will be assumed to be missing at random, i.e., conditional on the observed data the missingness is independent of the unobserved responses.

For continuous assay variables, overall differences between groups at a specific time point will be tested by a 2-sample t-test if the data appear to be normally distributed, or by utilizing the nonparametric Wilcoxon rank sum test if the data are not normally distributed. If a portion of the measurements are censored below the assay quantification limit, then the Gehan-Wilcoxon test will be employed. More sophisticated analyses employing repeated

measures methodology (for example, repeated measures ANOVA or generalized estimating equations) may be utilized to incorporate immune responses over several time points. However, inference from such analyses would be limited by the small sample size of this study. All statistical tests will be 2-sided and will be considered statistically significant if  $p \leq 0.05$ . Graphical descriptions of the longitudinal immune responses will also be given.

Some immunologic assays have underlying continuous or count-type readout that is often dichotomized into responder/nonresponder categories. For these assays, graphical and tabular summaries of the underlying distributions will be made. These summaries may be performed on transformed data (e.g., log transformation) to better satisfy assumptions of symmetry and homoscedasticity. If group comparisons in these underlying distributions reveal that differences are best summarized as a shift in the location of the distribution, then results will be presented in the form of group means (or medians) with associated confidence intervals and statistical tests for differences between groups as described above. If group comparisons in these underlying distributions reveal that differences are best summarized by a mixture model (i.e., responder and nonresponder subgroups are clearly identifiable) then results will be presented in the form of response rates with associated confidence intervals and statistical tests as described above.

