Enrollment in Groups 3 and 4 will be sequential. See Section 8.3 for dose escalation criteria.

Enrollment in Groups 5, 6, and 7 will occur simultaneously. See Section 8.4 regarding safety evaluation for moving from Part A to Part B.

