### 9.4 Accrual and sample size

Recruitment will target 156 healthy, HIV-uninfected adult participants.

Part A will consist of 4 groups. Groups 1 and 2 will be enrolled simultaneously with participants randomized to receive either *gag* DNA or placebo (Group 1), or *gag* DNA plus *IL-12* DNA (100 mcg) or placebo (Group 2) in a (10:2) ratio within each group. Groups 3 and

4 will proceed sequentially according to dose escalation rules outlined in Sections 8.3 and 14.7.5. Groups 3 and 4 will each enroll participants randomized to receive either *gag* DNA plus *IL-12* DNA (maximum tolerated dose, MTD) or placebo in a (10:2) ratio.

Part B will consist of 3 groups (Groups 5, 6, 7) and will follow Part A according to rules outlined in Section 8.4. Groups 5, 6, and 7 will be enrolled simultaneously and randomized to receive either *gag* DNA (1500 mcg) for both prime and booster vaccinations or placebo (Group 5), or *gag* DNA plus *IL-12* DNA (MTD) for both prime and booster vaccinations or placebo (Group 6), or *gag* DNA plus *IL-12* DNA (MTD) for prime and HIV CTL MEP for booster vaccinations or placebo (Group 7), each group with a (30:6) ratio for vaccine to placebo.

Note that study design blinds participants and site staff to vaccine or placebo arms of each group, but participants will not be blinded as to which group they are in.

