#### 9.4.1 Sample size calculations for safety

The goal of the safety evaluation for this study is to identify safety concerns associated with administration. Sample size calculations for safety are expressed in terms of the ability to detect rare events (e.g. serious adverse events (SAEs)).

The ability of the study to identify serious adverse experiences can be expressed by the maximum true rate of events that would be unlikely to be observed and the minimum true rate of events that would very likely be observed.

Specifically, for each vaccine arm of Part A (n=10), there is a 90% chance of observing at least 1 serious adverse experience if the true rate of such an event is at least 21%; there is a 90% chance that we would not observe at least 1 serious adverse experience if the true rate was no more than 1%.

For each vaccine arm of Part B (n=30), there is a 90% chance of observing at least 1 serious adverse experience if the true rate of such an event is at least 8%; there is a 90% chance that we would not observe at least 1 serious adverse experience if the true rate was no more than 0.35%.

Probabilities of observing 0 or 2 or more serious adverse experiences among groups of size 10 and 30 are presented in Table 9-1 for a range of possible true event rates. These calculations provide a more complete picture of the sensitivity of this study design to identify potential safety problems with the vaccine.

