#### 9.4.2 Sample size calculations for immunogenicity

In Part A, the precision with which response rates can be estimated, based on a sample of 10 vaccines, is limited. The standard error of the estimated response rates depends on the true underlying response rate but can be bounded by  $0.16 (= \sqrt{0.5 \times 0.5 / n})$ . Thus, the width of a 95% confidence interval for the response rate in any 1 arm will be no greater than 0.63 (i.e.,  $\pm 1.96 \times 0.16$ ).] In Part B, based on n=30, the standard error of the estimated response rates can be bounded by  $0.09 (= \sqrt{0.5 \times 0.5 / n})$ . Thus, the width of a 95% confidence interval for the response rate in any 1 arm will be no greater than 0.35 (i.e.,  $\pm 1.96 \times 0.09$ ).]

Table 1-2 below displays exact confidence intervals for several possible observed rates of response in Part B.

**Table 9-2 Exact 95% 2-sided confidence intervals for response rates based on observing a particular rate of responses in the vaccinees (n=30) in Part B.**

| Observed response rate(%) | Confidence interval
(n=30) |
|---------------------------|-------------------------------|
| 50                        | [31, 69]                      |
| 60                        | [41, 77]                      |
| 70                        | [51, 85]                      |
| 80                        | [61, 92]                      |
| 90                        | [73, 98]                      |

In Part B, there is limited power for a formal comparison of immunogenicity response rates between vaccine groups of size n=30 and, hence, formal comparisons were not listed in the objectives. For illustration, we include power calculations for comparison of response rates between vaccine groups (n=30) that can be distinguished with statistical power of 80% and 90% for an exact 2-sided test with a Type I error rate of 0.05 in Table 9-3. Note the sizes of the differences the trial is powered to detect are very large.

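### Section 9.5.4 lets a significant difference be declared between any pair of vaccine arms, although 17 of the 21 pairs are not concurrently randomised

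*Protocol*

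**What the plan says.** Section 9.5.4 first covers both Parts: "For Parts A and B, crude rates for each vaccine group will be calculated". In the next paragraph it gives the decision rule: "To compare the response rates of any two vaccine arms, a significant difference will be declared". The criterion is that zero lies outside a two-sided 95% interval for the difference between the two rates. It names no interval method and no subset of pairs. For continuous readouts the same section adds "All statistical tests will be 2-sided and will be considered statistically significant if" p is at most 0.05, again without saying which groups may be compared.

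The term used in the rule is not reserved for Part B. Section 9.4.1 speaks of "for each vaccine arm of Part A (n=10") and, in the same way, of Part B with n=30.

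On enrolment, the Schema has Groups 1 and 2 enrolling together and then states: "Enrollment in Groups 3 and 4 will be sequential". Part B follows Part A, and Section 9.4 says "Groups 5, 6, and 7 will be enrolled simultaneously and randomized".

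Section 9.4.2, writing about Part B, notes limited power at n=30 and says that "formal comparisons were not listed in the objectives". It neither withdraws nor narrows the rule in 9.5.4. Section 9.5 makes no formal multiplicity adjustment across specified scientific questions.

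**The concern.** Randomisation protects a comparison only between arms that were open to the same participants at the same time. As worded, the rule gives an IL-12 dose contrast such as Group 4 v Group 3, or a cross-Part contrast such as Group 6 v Group 4, the same standing as the randomised Part B contrasts. A difference caused by calendar period, or by another feature that changed with it, could then be reported as a significant product effect. IL-12 dose comparisons are a natural use of the Part A data, so the misreading is realistic. What is at stake is the interpretation of a secondary endpoint in a Phase I trial. The primary safety objective is not affected.

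**Working it through.** **1. The plan's own figures.** Section 9.4.2 bases Table 9-3 on an exact two-sided test at 0.05 with 30 v 30. Full enumeration of Fisher's exact test reproduces 12 of the 14 cells. The other two agree within rounding. For a first-group rate of 10% at 90% power, the stated 49 gives power 0.900 to three decimals, and the first whole percentage to reach the target is 50. For 70% at 90% power, the entry >99 corresponds to 100. The table is sound, but it covers 30 v 30 only. No power is given for 10 v 10 or 10 v 30, although the rule reaches those pairs.

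**2. Counting the pairs.** The enrolment cohorts (Schema; Sections 8.3, 8.4 and 9.4) are {1, 2}, {3}, {4} and {5, 6, 7}.

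- All pairs: 7 × 6 / 2 = 21.
- Concurrent: 1 pair in {1, 2} plus 3 pairs in {5, 6, 7} = 4.
- Not concurrent: 21 − 4 = 17. Of these, 6 − 1 = 5 lie within Part A and 4 × 3 = 12 cross the Parts.

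Counting 1 v 2 as randomised rests on simultaneous enrolment and on Section 9.6, which has blocks balancing across groups. Section 9.4 describes the 10:2 allocation as within each group. If that were the only randomisation, 1 v 2 would also drop out, so 17 is the cautious count.

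**3. What differs besides the product.**

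| Feature | Within Part A (5 pairs) | Across Parts (12 pairs) |
|---|---|---|
| Calendar period | differs | differs |
| ALT, AST, alkaline phosphatase limit (Table 7-1) | same | 1 × v 1.25 × upper limit of normal |
| IL-12 plasmid lot (Section 2.2) | same | differs where both arms contain it: 3 × 2 = 6 pairs |
| Vaccinations before the primary time point (Sections 8.7.2, 8.7.3) | 3 v 3 | 3 v 5 |

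**4. What a period effect would do.** The documents give no size for a drift, so these sizes are assumptions. With no product effect, the chance of a declaration is

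P = Σₐ Σ_b Bin(a; n₁, p₁) · Bin(b; n₂, p₂) · 1{rule declares at (a, b)}.

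Three versions of the rule are shown because the interval method is not named.

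| Sizes | True rates | Fisher | Newcombe | Wald |
|---|---|---|---|---|
| 10 v 10 | 20% v 20% | 0.008 | 0.030 | 0.091 |
| 10 v 10 | 20% v 30% | 0.021 | 0.058 | 0.136 |
| 10 v 10 | 20% v 40% | 0.058 | 0.131 | 0.246 |
| 10 v 30 | 20% v 20% | 0.023 | 0.036 | 0.117 |
| 10 v 30 | 20% v 30% | 0.051 | 0.061 | 0.184 |
| 10 v 30 | 20% v 40% | 0.138 | 0.181 | 0.329 |

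**5. Multiplicity, as a separate illustration.** Chance of at least one declaration when all arms share one true rate (10%, 20%, 30%, 50%) and there is no drift; one readout, 200,000 simulated trials.

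| Rule | All 21 pairs | 17 non-concurrent | 4 concurrent |
|---|---|---|---|
| Newcombe | 0.230, 0.361, 0.380, 0.431 | 0.198, 0.309, 0.335, 0.384 | 0.075, 0.138, 0.152, 0.165 |
| Wald | 0.686, 0.548, 0.558, 0.537 | 0.665, 0.498, 0.505, 0.501 | 0.176, 0.223, 0.223, 0.204 |
| Fisher | 0.153, 0.222, 0.253, 0.227 | 0.135, 0.196, 0.221, 0.186 | 0.026, 0.065, 0.078, 0.082 |

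This second table contains no period effect. It shows what many looks would do and does not measure the bias in step 4.

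**The case against.** The sentence says how a difference is judged once two arms are compared. It does not say that every pair will be compared. No section schedules a Part A dose comparison or a cross-Part comparison. Section 9.4.2 keeps formal comparisons out of the objectives, presents its power table as an illustration and offers ranking of the Part B groups instead. Section 5.1 says Part A samples are assayed only if Part B shows responses, and Appendix B leaves those assays to retrospective discretion. The cross-Part pairs share no primary time point unless optional Part B assays after the third dose are run. The lot change is one noncoding nucleotide said not to alter expression, and no document links the relaxed liver-enzyme limit to T-cell response.

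Much of this stands, and it rules out stronger readings:

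- A reader might infer that the protocol runs 21 tests with a family-wise error of 0.15 to 0.69. It does not schedule them, and doing without adjustment is an openly stated choice in Section 9.5.
- A reader might take those rates as the size of the non-concurrency problem. They assume no drift.
- A reader might see site imbalance among Part A groups in the start at US sites only (Section 8.2). That restriction applies alike to the first five participants of every Part A group.

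What the objection does not remove is the scope of the rule. Conditional or discretionary testing lowers how often a non-concurrent contrast is made, but does not protect it once made. If the rule was meant for Part B only, as the 30 v 30 table may suggest, the sentence does not say so.

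**Conclusion.** The point holds in a limited form. The protocol permits a declaration of significance for 17 of 21 pairs that are confounded with calendar time; 12 of these also differ in eligibility limits and in doses at the primary time point. The counts follow directly from the enrolment plan, taking 1 v 2 as concurrently randomised. The amount of bias is unknown. Under an assumed drift from 20% to 40% with no product effect, the chance of a declaration is 0.06 to 0.25 for 10 v 10 and 0.14 to 0.33 for 10 v 30, against 0.01 to 0.09 and 0.02 to 0.12 without drift. Because the endpoint is secondary and the protocol itself plays down formal comparisons, this is a cheap improvement and not a fault that threatens the trial.

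**What to change.** In Section 9.5.4, restrict the decision rule to concurrently randomised vaccine arms: 5 v 6, 5 v 7 and 6 v 7 in Part B, and 1 v 2 in Part A. Apply the same limit to the tests at p of 0.05 or less on continuous readouts. Report every other contrast (those between non-concurrent Part A groups, and all Part A v Part B contrasts) as an estimate with a 95% confidence interval, labelled non-randomised, with no declaration of significance.

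The cost is a small wording change in one section. No sample, visit or participant changes, and every estimate can still be reported. The downside is that the Part A IL-12 dose contrasts other than 2 v 1 lose a significance statement; with n=10 per arm they carry little information in any case. A Holm procedure, or a shorter list of named contrasts, is an optional matter of preference and not part of this correction: the argument from randomisation gives no reason to demote 7 v 5.

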### **8.7.1 Humoral immunogenicity studies (HVTN)**

#### **8.7.1.1 Binding antibodies by ELISA (Part B only)**

Binding antibodies to commercially available Gag will be assessed at the HVTN Laboratory Program by ELISA using single serum dilutions (1/50 or 1/100) on samples from all study participants taken at baseline and 2 weeks after the fourth and fifth vaccination visits. Any of the time points that yield positive results, defined as an OD of  $\geq 0.2$ , in the initial ELISA may be subject to endpoint titration ELISA employing 6 (2-7-fold) serial dilutions of serum beginning at a 1/50 or 1/100. Additional ELISA may be performed in all participants using cryopreserved samples if positive responses are observed at the primary immunogenicity time point (see Appendix C).

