### **8.7.3 Cellular immunogenicity studies for Part B (HVTN)**

#### **8.7.3.1 IFN- $\gamma$ ELISpot**

Bulk T cell responses will be assessed by IFN- $\gamma$  ELISpot using cryopreserved PBMC stimulated overnight with synthetic peptide pools that span the proteins encoded by the vaccine constructs. ELISpot assays will be performed at baseline and ELISpot assays will be performed at baseline and at two weeks post final (fifth) vaccination. Additional time points may be assayed if positive responses are observed at the primary immunogenicity time point (see Appendix C). Responses will be reported as number of spot forming cells per  $10^6$  cells/well recognizing any specific peptide pool.

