#### **8.7.3.2 Intracellular cytokine staining (ICS) for Part B**

Flow cytometry will be used to examine HIV-specific CD4+ and CD8+ T cell responses using ICS following stimulation with synthetic HIV peptides that span the proteins encoded by the vaccine construct. ICS assays will be performed at baseline and ELISpot assays will be performed at baseline and at two weeks post final (fifth) vaccination. Additional time points may be assayed if positive responses are observed at the primary immunogenicity time point (see Appendix C). Responses will be reported as percentages of CD4+ or CD8+ T cells recognizing any specific peptide pool.

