**Table 9-3 Minimum detectable differences in response rates between 2 groups (of size 30)**

| True response rate 1 st group (%) | Minimum detectable response rate 2 nd group (%) |           |
|----------------------------------------------|------------------------------------------------------------|-----------|
|                                              | 80% power                                                  | 90% power |
| 10                                           | 44                                                         | 49        |
| 20                                           | 58                                                         | 63        |
| 30                                           | 69                                                         | 74        |
| 40                                           | 78                                                         | 83        |
| 50                                           | 86                                                         | 90        |
| 60                                           | 93                                                         | 96        |
| 70                                           | 98                                                         | >99       |

An alternative to formal comparisons of groups in Part B is to rank the vaccine groups by their immune response rates. We assess the reliability of this study to select the best group

with respect to the magnitude of their response rates. See Table 9-4 below. Each line in the table shows the results of N=40,000 simulated datasets generated using two (best/ next best) different binomial probabilities for 3 groups of size 30, with the best (highest) response probability used to generate data for one group and the next best response probability used to generate data for the remaining 2 groups. These simulations illustrate the probability of correctly selecting the highest response group 90% (or 80%) of the time [101] given the assumed parameters (best response probability, difference between best and next best).

**Table 9-4 Probability of 90% (80%) correct selection of regimen with highest immunology response (n=30 per group) among 3 groups**

| Next Best response probability (%) | Best response probability (%) | Difference |
|------------------------------------|-------------------------------|------------|

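### The default between-arm tests of ELISpot and ICS magnitude are valid but leave the scheduled Day 0 value unused; adjusting for it could add a little precision, depending on an unstated correlation

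*Protocol*

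**What the plan says.** Protocol section 9.5.4 fixes the default comparison of continuous readouts: "overall differences between groups at a specific time point will be tested by a 2-sample t-test if the data appear to be normally distributed". A Wilcoxon rank sum test replaces it for non-normal data. For values under the assay limit the rule is: "If a portion of the measurements are censored below the assay quantification limit, then the Gehan-Wilcoxon test will be employed". No baseline term is named in any of the three. The tests are two-sided at 0.05.

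The Day 0 value is planned. For Part B, section 8.7.3.1 says "ELISpot assays will be performed at baseline and at two weeks post final (fifth) vaccination", and section 8.7.3.2 says "ICS assays will be performed at baseline". Appendix C allots Day 0 blood to both assays (60 mL and 40 mL), and again at Visit 11, two weeks after the fifth vaccination.

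Baseline or other visits can enter in two places. Section 9.5.4 permits repeated-measures ANOVA or generalized estimating equations over several time points as an option, with a caution about the small sample. Section 9.5.4.1 puts baseline predictors into secondary models, but only if more than 20% of participants have a missing value.

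**The concern.** A post-vaccination reading may include some of the participant's own background signal, and Day 0 measures that background with the same assay. A test that ignores Day 0 leaves the shared part in the error term, along with any chance difference in background between arms of 30. Adjusting for Day 0 removes whatever part is shared.

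Part B is described in section 5.1 as a regimen optimization and selection design, and response magnitude is among the things the programme wants to learn. The default tests of magnitude might therefore be run with wider intervals than the collected data allow. At stake is the precision of a secondary analysis. Its validity and the safety objectives are not affected.

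**Working it through.** **Inputs**
- Arm size: 30 against 30 for vaccine-arm comparisons in Part B (Schema; section 9.4.2).
- Level: two-sided 0.05 (section 9.5.4).
- Standard deviation and effect size of continuous readouts: not stated, so differences are in SD units.
- Correlation rho between Day 0 and post-vaccination value: not stated. Assumed range 0 to 0.5.

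**The plan's own figures.** The protocol gives no power figure for continuous readouts. Its nearest figures are the response rates in Table 9-3, stated "for an exact 2-sided test with a Type I error rate of 0.05". Full enumeration of Fisher's exact test with 30 against 30 reproduces the 80% column in every row (power 80.3% to 82.5% at the tabled rates). The 90% column also reproduces, except that the 10% row needs 50 and not 49 on strict rounding (power at 49 is 90.0% to one decimal). The >99 entry is consistent, since power at 99 is 86.4%. The point below alters none of these figures.

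**Unadjusted t-test.** With 58 degrees of freedom and noncentrality d x sqrt(30/2), power is 80% at d = 0.736 SD.

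**Adjusting for Day 0.** ANCOVA multiplies the variance of the arm difference by

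V = (1 - rho²) x (1 + 1/56),

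where 1/56 = 1/(2 x 30 - 4) is the average cost of estimating the slope. The effective arm size is 30/V. Power at d = 0.736 uses noncentrality d x sqrt(15)/sqrt(V) with 57 degrees of freedom.

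| rho | V | 30/V | Power at 0.736 SD | Difference detectable with 80% power |
|---|---|---|---|---|
| 0 | 1.018 | 29.5 | 79.3% | 0.742 SD |
| 0.1 | 1.008 | 29.8 | 79.7% | 0.739 SD |
| 0.2 | 0.977 | 30.7 | 80.9% | 0.727 SD |
| 0.3 | 0.926 | 32.4 | 82.9% | 0.708 SD |
| 0.5 | 0.763 | 39.3 | 89.4% | 0.643 SD |

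Break-even is where 1 - rho² = 56/57, so rho = sqrt(1/57) = 0.13.

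**Two covariates.** If an indicator for a Day 0 value at the assay floor is added, the cost factor becomes 1 + 2/55 = 1.036. If the indicator explains nothing further, the effective arm size at rho 0 is 30/1.036 = 28.9, power there is 78.5%, and break-even moves to sqrt(2/57) = 0.19.

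**Change from baseline.** A plain change score has variance ratio 2(1 - rho): 2.0 at rho 0, 1.4 at 0.3 and 1.0 at 0.5. It loses precision whenever rho is below 0.5.

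**The case against.** The strongest reply is that nothing here is wrong. An unadjusted comparison of randomized arms is valid, formal comparisons between vaccine groups are not among the objectives (section 9.4.2), and a covariate can be added in an SAP. All of that stands, and it makes this a suggestion for improvement. It does not remove the point, because section 9.5.4 names the default tests and an SAP that follows it would carry them over.

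The second reply is that the benefit is assumed. This also stands. Participants are HIV-seronegative (section 7) and recipients of HIV vaccine in an earlier trial are excluded (Table 7-2), so the Day 0 readout should be mostly background and rho is plausibly low. Below about 0.13 adjustment loses slightly. A reader might infer that precision is being thrown away at no cost; the table does not support that.

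The third reply is that the data may not suit a linear model. Section 9.5.4 expects censoring and possibly a responder/nonresponder mixture, and Day 0 itself may often sit at the assay floor. This stands too. Log-scale ANCOVA needs a rule for such values, and the gains above do not carry over to a rank-based model.

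**Conclusion.** The point holds as a small efficiency improvement. By default, the tests of ELISpot and ICS magnitude do not use the Day 0 value. Relative to a t-test with 80% power, adjustment for one covariate is worth between -0.7 points (rho 0) and about +9 points (rho 0.5), with the low end more likely. This rests on the assumed rho, arms of 30, complete data and a roughly linear relation on the analysis scale.

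Three stronger readings are not supported:
- A reader might infer that the plan can use only the post-vaccination value. Sections 9.5.4 and 9.5.4.1 allow other routes, one optional and one conditional.
- A reader might link this to the protocol's remark that detectable differences are very large. That remark concerns response rates in Table 9-3, not continuous readouts.
- A reader might extend the point to binding ELISA, with samples "taken at baseline and 2 weeks after the fourth and fifth vaccination visits". ELISA is not an endpoint in section 9.3.2. It starts at a single dilution, and titration may follow only where the optical density is at least 0.2, so a Day 0 titre may not exist.

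**What to change.** In section 9.5.4, before the unblinded immunogenicity analysis described in section 9.5.6, pre-specify for ELISpot and ICS magnitude:
- an ANCOVA on a log scale with a stated offset for zeros, with terms for arm, Day 0 value, and an indicator for Day 0 at or below the quantification limit;
- a proportional-odds model with the same terms where the outcome is non-normal or censored;
- the planned unadjusted test, reported alongside.

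Do not substitute a plain change from baseline.

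The Day 0 assays are already scheduled, so the cost is analysis wording and a few lines of code. The statistical cost is one or two degrees of freedom. If rho is near 0, the loss is about 0.7 power points with one covariate and 1.5 with both. No sample size, power figure or visit changes.
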